### Study design

The study duration spans from February, 2015 to June, 2017 (Fig. 3). The longitudinal cohort study consists of three cross-sectional surveys (baseline, mid- and final follow-up). At each survey time point, disease status, anthropometry and levels of physical fitness, cognitive performance and psychosocial health are measured. After each survey, infected individuals are either treated with anthelminthics (400 mg albendazole, single dose) for soil-transmitted helminths [15] and/or referred to local clinics for the management of other intestinal parasite infections. Based on results from the baseline survey, a package of setting-specific interventions is designed together with local students, teachers, school volunteers and parents. The intervention package consists of three main components:

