**Fig. 3 Fig3:**
[figure not shown]
A pictorial display of the design and timeline of the DASH study

(i)Physical activity [9, 16]: Regular physical activity opportunities, including two physical education (PE) lessons a week, weekly dancing-to-music classes, and in-class activity breaks will be incorporated into the main school curriculum and a physical activity friendly school environment will be created. These approaches could help improve children’s physical fitness, and positively affect their psychosocial health [17–21].(ii)Health education [22]: A series of classroom-based lessons will be developed to help increase the awareness for intestinal parasite infections among the schoolchildren and educate them on treatment and prevention methods, such as proper hygiene, sanitation habits and the importance of consuming clean water and food. It is also planned that schoolchildren will produce a theatre play to convey key messages they have learnt through the health education.(iii) Nutritional interventions: A series of classroom-based lessons will be developed to help increase the awareness of the importance of healthy nutrition. In addition, an analysis of the school feeding programme will be done to identify ways to improve their current diet to be healthier. The schoolchildren will also be given a ready to use supplementary food (RUSF) in the form of an enriched lipid-based paste. The cooks in the schools will also be trained in basic nutrition and hygiene during preparation of the school meals.

The interventions will be embedded within the longitudinal study and be implemented in half of the schools, while the remaining schools will serve as controls. The intervention schools were either selected due to the soil-transmitted helminth prevalence, number of Grade 4 learners, geographical location and affiliation to a particular ethnic group or commitment of teachers or school staff. Implementation of the interventions will take place twice; in July-September, 2015, after the baseline survey, and in February-March, 2016, after the first follow-up. The first follow-up will allow the implementation feasibility of the designed interventions to be determined through focus-group discussions with teachers and students, while the subsequent surveys will allow assessing their impact on the measured health parameters.

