### Sample size

The sample size calculation for the study was based on achieving sufficient precision in estimating the prevalence of soil-transmitted helminth infections. We conducted our calculation under the following assumptions for the cross-sectional baseline study:i)a prevalence of soil-transmitted helminth infections, *p*, of approximately 3 %;ii)an average number of children per school, *B*, of 150; andiii)an intra-class correlation coefficient for the clustering of outcomes within schools, *ICC*, of 0.15.

Requiring the standard error of the respective prevalence, *SE*, not exceeding 2.5 %, we obtained a necessary sample size *n* of 1088 children, using the formula [23]$$ n\kern0.5em \cdot \ge \frac{p\cdot \left(1-p\right)}{S{E}^2}\left(1+\left(B-1\right)\cdot ICC\right) $$

As a consequence, eight clusters (schools) will be needed considering the fact, that with a total of 1200 children from eight schools, we can accommodate 10 % loss to follow-up.

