### Data analysis

The primary objectives of the statistical analysis will be to assess (i) the prevalences of infections and conditions, and their associations with physical fitness, nutritional status, cognitive performance and psychosocial health at baseline and over time; and (ii) the effects of interventions on disease status and other health parameters. The secondary objective will be to assess the feasibility and acceptability of the health interventions implemented.

Parasitological status will be assessed in terms of prevalence and intensity of infection with specific parasite species and the extent of multiparasitism. Clinical and anthropometric indicators, physical fitness, cognitive performance and psychosocial health scores will be characterised by their mean and standard deviation if they are normally distributed and by their median and interquartile range otherwise. Questionnaire data pertaining to the psychosocial health will be expressed as percentages. All indicators will be compared between physically fit/non-infected and physically unfit/infected children and between intervention and control schools.

To assess the effects of the different interventions on the parasitological status, clinical and anthropometric indicators, physical fitness, cognitive performance and psychosocial health, the following statistical procedures will be employed:(i)Mixed logistic regression models with random intercepts for schools will be used to compare binary data, such as parasitological status and clinical indicators, between the intervention and control groups.(ii)Linear mixed models with random intercepts for schools will be used for numeric data, such as anthropometric measurements, physical fitness, cognitive performance, and psychosocial health scores and haemoglobin concentration measurements.These models will include sex and age of the child, socioeconomic status of the parents or health status or fitness at the baseline survey as well as variables which were not perfectly randomised and might therefore act as confounders. Moreover, as intervention effects might depend on baseline characteristics of the child, stratified analyses and analyses involving interaction terms will be performed. The potential effect modifiers tested include sex, age, socioeconomic status of the parents or health status or fitness at the baseline survey.

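### The covariate rule joins its items by 'or' and does not commit each outcome model to the baseline value of its own outcome, which matters with eight purposively allocated schools

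*Protocol article*

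**What the plan says.** The Data analysis section of the protocol article sets out two families of models for the intervention effect. For binary outcomes: "Mixed logistic regression models with random intercepts for schools will be used to compare binary data, such as parasitological status and clinical indicators". For numeric outcomes: "Linear mixed models with random intercepts for schools will be used for numeric data, such as anthropometric measurements, physical fitness, cognitive performance", along with psychosocial scores and haemoglobin.

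One sentence then fixes the covariates for both families: "These models will include sex and age of the child, socioeconomic status of the parents or health status or fitness at the baseline survey". It continues: "as well as variables which were not perfectly randomised and might therefore act as confounders". The list of potential effect modifiers that follows uses the same 'or'.

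The Study design section says of the data: "At each survey time point, disease status, anthropometry and levels of physical fitness, cognitive performance and psychosocial health are measured". On allocation, it says that the interventions will "be implemented in half of the schools, while the remaining schools will serve as controls", and describes the choice of schools as follows: "The intervention schools were either selected due to the soil-transmitted helminth prevalence, number of Grade 4 learners, geographical location", with ethnic affiliation and staff commitment as further grounds. Allocation was therefore not random, and helminth prevalence, one ground for selection, is itself an outcome.

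**The concern.** The article states an adjustment rule, but the rule does not settle what enters a given model. Taken literally, 'or' makes socioeconomic status, health status and fitness alternatives. A model for the d2 attention score with sex, age and socioeconomic status complies. So does one with sex, age and baseline fitness. Neither contains the child's d2 score at baseline.

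In a non-random comparison of eight schools, the outcome's own baseline value is the main available protection against arms that already differed at the start, and a main source of precision. If it is left out, a baseline gap carries into the follow-up comparison in proportion to the outcome's stability over time, and could be reported as an intervention effect or mask one. A loose rule also leaves room to choose covariates after the data are seen.

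**Working it through.** **1. Which outcomes does the wording cover?**

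| Outcome group | Own baseline among the named covariates? |
|---|---|
| Parasitological status, clinical indicators | Can be, as baseline health status |
| Physical fitness | Can be, as baseline fitness |
| Anthropometry, psychosocial scores | Only if health status is read broadly |
| d2 test, school grades, national assessment scores | Not clearly; only through the open confounder clause |

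Even where it can be covered, the 'or' does not require it.

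**2. The article's own calculation.** The only sample-size figure concerns the precision of baseline helminth prevalence. With p = 0.03, SE = 0.025, B = 150 and ICC = 0.15:

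n ≥ 0.03 × 0.97 / 0.025² × (1 + 149 × 0.15) = 46.56 × 23.35 = 1087.2, rounded up to 1088.

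This reproduces the stated 1088. It does not address the intervention comparison and does not change here.

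**3. Inputs for the illustration.**
- From the article: four schools per arm (half of eight); m = 125 children per school (about 1000 / 8); ICC = 0.15, which is given for helminth infection and applied here to other outcomes as an assumption.
- Assumed: a baseline-to-follow-up correlation r of 0.3 to 0.8, equal at child and school level. The article gives no value.

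**4. Standard error of the difference between arms, in SD units.**

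Without own baseline: √{(2/4) × [0.15 + 0.85/125]} = √(0.5 × 0.1568) = 0.280.

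With own baseline: 0.280 × √(1 − r²). The detectable difference is SE × (t₀.₉₇₅ + t₀.₈₀) on 6 degrees of freedom, for 80 % power.

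| r | √(1 − r²) | SE | SE reduction | Detectable difference (SD) |
|---|---|---|---|---|
| none | 1 | 0.280 | – | 0.94 |
| 0.3 | 0.954 | 0.267 | 5 % | 0.90 |
| 0.5 | 0.866 | 0.242 | 13 % | 0.81 |
| 0.7 | 0.714 | 0.200 | 29 % | 0.67 |
| 0.8 | 0.600 | 0.168 | 40 % | 0.56 |

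The article's Discussion fears 30–40 % loss to follow-up. At 35 %, m is about 81, and the unadjusted SE is 0.283 with a detectable difference of 0.95 SD. The result hardly moves, because the number of schools dominates.

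**5. Bias if the own baseline is omitted.** A baseline gap of d SD leaves about r × d at follow-up. For d = 0.3: 0.3 × 0.3 = 0.09; 0.5 × 0.3 = 0.15; 0.7 × 0.3 = 0.21; 0.8 × 0.3 = 0.24 SD.

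A gap of 0.3 SD is not extreme. By the formula in step 4, chance alone gives baseline gaps with a standard deviation of about 0.28 in a four-versus-four comparison, before any purposive selection.

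**The case against.** The strongest reply is that the sentence excludes nothing. A reader might infer that the plan uses health status or fitness in place of each outcome's own baseline. The text does not say so: for parasitological, clinical and fitness outcomes those terms may be the own baseline. A reader might also infer that baseline imbalance is ignored. That is not supported either, since the closing clause on possible confounders could admit a baseline outcome that differs between arms. Both points stand. But the clause names no variable, makes inclusion depend on a judgement of imbalance, and refers to imperfect randomisation where none is described. It permits the own baseline without requiring it, and secures no precision where the arms look balanced.

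Second, an article need not list covariates outcome by outcome; a full protocol or analysis plan may do so. That is fair for detail. Here, however, the article does state a rule, and the rule as worded is ambiguous.

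Third, the size is illustrative. The values of r are assumed. The comparison is with a model without baseline covariates, whereas the plan already adjusts for some, and any correlation between arm and baseline value would reduce the gain. This stands, and the SE reductions should be read as upper bounds for a given r.

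Fourth, not every outcome is certain to have a baseline value. The Study design section lists domains, while the Assessment methods section lets each survey use a selected combination of procedures. This stands too, and limits the fix.

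**Conclusion.** The point holds as a defect of specification. The rule does not commit each model to its outcome's own baseline value and lets socioeconomic status drop out. The gap is clearest for d2, school grades and national assessment scores, and extends to psychosocial and anthropometric outcomes on a narrow reading of health status.

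If the own baseline is omitted, the bias is about r times the baseline gap, or 0.09 to 0.24 SD for a 0.3 SD gap, and the standard error is larger than it need be by an amount that adjustment would cut by at most about 5 % to 40 %. These figures rest on the assumed r of 0.3 to 0.8, on an ICC of 0.15 carried over from the prevalence calculation, and on 125 children in each of eight schools. They show what is at stake and do not establish that any planned estimate is biased by that amount.

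It might seem to follow that baseline health status and fitness should be kept only for the effect-modification analyses. The article points the other way. Schools were selected partly on helminth prevalence, and the Background hypothesises that infection affects fitness, cognition and nutrition, so baseline infection is a plausible confounder and should stay in the models.

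**What to change.** Replace the covariate sentence with a commitment along these lines: every follow-up model includes the child's baseline value of the same outcome wherever that outcome was measured at baseline, together with sex, age **and** socioeconomic status; baseline infection or health status, and other named variables that differ between the arms, are retained as confounders. Where an outcome has no baseline value, say so and name the covariates used instead.

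The cost is small. It takes a sentence and no new measurements. Missing baseline values can be handled by the multiple imputation already foreseen in the Discussion. A school-mean baseline term is optional, because it uses one of only six between-school degrees of freedom. The report should still acknowledge that own-baseline adjustment does not remove confounding by unmeasured differences between schools.

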### Ethical approval and considerations

Ethical approval for the study has been obtained from the Ethics Committee Northwest and Central Switzerland (EKNZ) in Basel, Switzerland (reference no. 2014–179; obtained on 1 August 2014), and the following ethics committees in Port Elizabeth, South Africa:(i)NMMU Human Ethics Committee (Human) (reference no. H14-HEA-HMS-002; obtained on 4 July 2014);(ii)Eastern Cape Department of Education (obtained on 13 August 2014); and(iii) Eastern Cape Department of Health (obtained on 7 November 2014).

Besides obtaining written informed consent, confidentiality of the study participants will be ensured by giving each participant a unique project-ID number so that all collected data of the schoolchildren will remain anonymous. Data will be used exclusively for scientific research and samples will be discarded after laboratory analyses have been completed. Paper records of the study are kept in locked cupboards in South Africa, accessible only by the main investigators. After 5 years, these records will be destroyed. Data entered into computerised files will be accessible only to authorised investigators or medical personnel directly involved with the study. At the end of the project, successful and appropriate interventions will be provided to the control schools so that the whole community can benefit from this project.

## Discussion

The baseline survey of this study has been conducted in February-March 2015. Subsequently, eight schools, with approximately 1000 schoolchildren, were selected for the study. During this first survey time point, several challenges were met and needed to be addressed. First, the study is conducted in impoverished and harsh environments, where illiteracy and violence are common [58, 59]. In these challenging socioeconomic conditions, the recruited schoolchildren may often be subjected to the lack of sufficient care or neglect by their parents [60–62]. As such, it was difficult to obtain support and written informed consent from the parents/guardians even if the schoolchildren have provided their oral assent. To address this issue, we prepared and conducted several pre-study workshops in the selected schools. The study purposes were explained in detail to the school principals, teachers and parents/guardians, in order to garner their strong support. We also adapted our study as much as possible in response to ideas voiced by teachers and parents to tailor the study further to the needs of the people concerned. Second, three languages, namely Afrikaans, Xhosa and English, are being spoken by the communities in the study area. For example, certain schoolchildren might prefer to speak and write in English, while others from the same school prefer Afrikaans. In addition, Xhosa-speaking children often preferred the tests to be administered in English, with explanations in Xhosa. This proved to be challenging when questionnaires were administered. Furthermore, although the questionnaires were pre-tested with some schoolchildren, the content of the questionnaires employed, particularly the ones focusing on psychosocial health indicators, did not fully match the educational level of the schoolchildren, making it hard for them to understand and answer the questions. To address these issues, we employed native speakers to perform the translation and to pre-test the translated questionnaires among teachers and students before the start of the study. During the actual administration of the questionnaires, we had the help of teachers and school volunteers to explain the questions to the children in their preferred language.

During our sample size calculation, we accounted for a 10 % loss to follow-up. Moving forward with the follow-ups and second phase of intervention, we might expect a more substantial loss (30-40 %) to follow-up as people show considerable mobility in this setting. We will address the potential bias resulting from differential loss to follow-up using inverse probability weighting, i.e. by assigning each follow-up participant the inverse of their prior probability of participation in the follow-up as weight in the follow-up analyses. In addition, multiple imputation will be used to deal with missing data where appropriate. However, it is difficult to predict the extent of the movement of people and hence, our presumed loss to follow-up might not be accurate.

Based on the obtained results, we have designed the health interventions together with local principals and teachers. Such collaboration is aimed at bolstering a sense of community ownership and empowerment, where the community feels that they are taking steps to improve the health of their children. We hope that this approach will further encourage the continued participation of the children and their parents/guardians during the study and sustained use of the interventions after the study has ceased.

In conclusion, the DASH study described here will provide a snapshot on the status of intestinal parasite infections and risk factors for diabetes and hypertension in selected disadvantaged primary schools in Port Elizabeth, South Africa. To our knowledge, such data are currently not available, and hence, our study fills an important void and generates new local evidence. By linking children’s parasitic infection status with the physical fitness, nutritional status, cognitive performance and psychosocial health, this wealth of information will help shed new light on the health consequences incurred by the children and provide guidance for further health interventions in this area. Implementation of setting-specific interventions within the longitudinal study will further highlight the feasibility and scalability of these health interventions in the study area.
